### Randomisation

When, as in our study, specific prognostic factors may influence outcomes, the best way to ensure a balanced distribution of participants across groups is to use an allocation by a minimisation process [30]. Accordingly, participants are stratified to one of the three study groups according to on their age and the severity of their tinnitus [31]. Age is included as a prognostic factor. This is based on the assumption that neurofeedback utilises the brain’s ability to reorganise itself functionally and/or structurally [32, 33]. With the current knowledge, evidence favours the hypothesis that younger individuals have greater neuroplastic potential [34] compared to older individuals. This is partially because of the association between increasing age and functional and structural brain deterioration [35, 36]. However, it would be false to believe that this deterioration affects all individuals to the same degree. With increased age comes large individual differences in brain health [34]. These differences are already apparent by the time people reach their mid-fifties [35]. Taken together, these observations have led to the following stratification categories for age in the present study: 1) ≤ 55 years; 2) > 55 ≤ 64; 3) > 64 ≤ 69; and 4) > 69. Given the conservative inclusion criterion on the primary outcome variable (18 ≥ THI score pre-intervention ≤100), stratifying participants into sub-groups based on the tinnitus distress classification by McCombe and Baguley [31] is considered a sensible option. This ensures a balanced distribution of the range of THI scores across the three groups. Importantly, this reduces the risk of heterogeneity of variance affecting the between-group outcome analysis. Thus, participants are stratified to one of four levels of tinnitus distress: 1) mild (THI 18–36); 2) moderate (THI 38–56); 3) severe (THI 58–76); and 4) catastrophic (THI 78–100).

Allocating participants to one of the three groups is performed by a researcher independent of the study. This individual, trained in the minimisation programme Minim [37], will subsequently inform the research team about the group allocation of each participant. A group allocation list is kept in a separate and password secured Excel file on the local drive of the independent researcher’s PC.

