### Interventions

#### Neurofeedback training groups

The neurofeedback training sessions are designed identically for the ADR and the BTR sessions. Both training sessions will be applied unidirectionally, with the aim of a) decreasing the ADR by an increase of alpha [8–12 Hz) and/or a reduction of delta (2–4 Hz) and b) decreasing the BTR by inhibiting theta (4–8 Hz) and/or reinforcing beta (13–20 Hz) activity bilaterally over the fronto-central cortex (FC1, FC2, F3 and F4).

During each neurofeedback (NF) training session, EEG and electromyography (EMG), as well as a vertical and horizontal electrooculogram (EOG), are recorded with Ag/AgCl-sintered ring electrodes with impedances kept below 5 kΩ using a 13-channel DC-amplifier (THERA PRAX®MOBILE, Neurocare GmbH, Ilmenau, Germany; > 10 Gohm input impedance) and a sampling rate of 256 Hz. EEG electrodes are placed at F3, F4, FC1 and FC2 in accordance with the 10/10 electrode placement system [38] using an elastic electrode cap (EasyCap, Woerthsee-Etterschlag, Germany). Reference and ground electrodes are attached to the right and left mastoid, respectively. The electrode montage is identical to previous neurofeedback studies in tinnitus [14, 39] to guarantee comparability with former research. EMG is recorded with two electrodes placed at the upper descending part of the M. trapezius. To reduce artefacts produced by eye movements, a real-time EOG is recorded simultaneously using four electrodes (two electrodes at external canthi, and two electrodes at infra- and supraorbital sides). Eye movements are removed from the feedback signal during the training using an online ocular correction as described by Schlegelmilch and Markert [40]. In addition, all signals acquired during neurofeedback training are stored as raw signals for later offline processing without any calibration or filtering.

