##### Training outcomes

To keep track of individual learning curves during training, we will analyse the ADR and BTR for each participant within and across sessions. However, session 1 will be discarded because it is assumed that participants will have to habituate to the setting. On the one hand, monitoring and encouraging learning will be performed by the trainers. On a patient monitor, the trainer can keep track of training progression as the percentage decrease in the BTR or ADR compared to the individual baseline for each training block.

On the other hand, the total number of successful trials per training block is used to guide either the upwards or downward adjustment of the training thresholds. Dependent measures include the mean training level over the training blocks within a session (%), the best run of each session (maximum training level) and the total number of obtained rewards per session. Furthermore, electrophysiological training raw data gathered with the THERA PRAX® MOBILE described previously will be analysed offline with Brain Vision Analyzer v2.0 (Brain Products GmbH, Gilching, Germany).

*Preprocessing:* Data are first band-pass filtered with Butterworth zero-phase filters between 0.1 Hz and 80 Hz with slopes of 24 dB/octave at the low and 48 dB/octave at the high cut-offs. To eliminate possible line noise, the data are further refined using a band-rejection filter with a central frequency of 50 Hz, a bandwidth of 1 Hz, and a slope of 24 dB/octave. For ocular correction, we will use Gratton and Coles’ [59] algorithm, as implemented in Brain Vision Analyzer software. Using a semi-automatic raw data inspection procedure, the recorded data from the training blocks will be screened for artifacts. Planned criteria for artifact screening will be as follows: maximal voltage step of 50 μV/ms, maximal amplitude of ±100 μV, maximum allowed difference of 150 μV in each segment, values greater than 200 μV per 200 ms interval and activity below 0.5 μV in a 50-ms period as the criteria. A total of 100 ms of data will be removed before and after any detected artifacts. A thorough visual inspection will be performed to remove any possible remaining artifacts (i.e., muscle movements and short drifts or jumps over single or multiple electrodes) from the signal.

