#### Data management and monitoring

Upon registration on the web platform, participants are assigned a computer-generated study code, which will follow them throughout the trial. All collected data are stored and pseudonymised in locked cabinets or as computer files. The pseudonymisation allocation list is kept separate from the pseudonymised data and deleted upon completion of the trial. Participants will be informed of this procedure. Only people who have signed a confidentiality agreement and are part of the research team have access to the data collected in the study.

The study’s assessment questionnaires are answered online. All necessary precautions have been taken to ensure data protection and security. All data exchanged between participants and the online system are encrypted prior to transmission and storage. The online system is managed and hosted by the IT Department of Linköping University (Sweden). No entries in the form of video or sound recordings, which could make it possible for third parties to identify the participants, are registered. Until the pseudonymisation allocation list is deleted, participants can ask for their data to be deleted at any time upon stating their assigned code. Lastly, data collected during the study are kept for 10 years before being deleted.

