Although double-blinding is considered the gold standard in randomised controlled trials, this study is non-blinded. Some proponents of neurofeedback argue that double-blinding in neurofeedback poses a significant challenge [69] and that the field is not yet mature enough to embrace the double-blind design [70]. The main technical challenge in the double-blind design in neurofeedback is that it necessitates the use of an automatic threshold setting in training. Thresholds in neurofeedback are used to reward behaviour and thereby shape it in the desired direction. When automatic threshold procedures are used, reward thresholds are adjusted moment by moment to ensure rewards for a certain percentage of time based on the previous averaged period, e.g., 15 s. However, if overall performance deteriorates, reward thresholds are adjusted downwards to adapt to the new output level. In doing so, despite a deterioration in performance, rewards are still elicited. The consequence of this is that behavioural shaping, the crucial goal in neurofeedback [69], is hampered. When this happens, learning processes are impaired [18, 69, 71, 72]. As a result, given this consideration whilst also acknowledging the absence of universal consensus on the matter, we opted for a design in this study in which only participants undergoing neurofeedback are blinded to their intervention.

The decision to use a between- rather than within-subject design was made only after several discussions and reflections. In the end, a between-subjects design was decided upon for two reasons. First, participation in this study requires a considerable time investment. In the within-subjects design, participants would have to set aside at least 8 weeks, spaced over two 4-week periods, with two to three training visits to the department per week. This factor, we feared, would increase the risk of participant drop out. Second, when the effects of a condition are expected to be persistent, a risk of carrying it over to the second condition exists, which may confound the outcomes [73]. Therefore, although this type of study requires a larger number of participants, we opted for the between-subjects design.

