### Limitations

The intent-to-treat statistical method applied in the study is particularly vulnerable in relation to treatment adherence and drop-out. The willingness of participants to complete all outcome measures, independent of their status in the trial, is crucial to avoid the distortion of study results. To maximise treatment adherence and minimise drop-out in the present study, based on recommendations in the literature (e.g., [43–45]), several steps have been taken to minimise the risk.

The non-blinding of therapists in the neurofeedback conditions mean the outcomes are more susceptible to the experimenter effect. This term covers situations in which the experimenter, with awareness of the components of interventions, unconsciously or unwittingly behaves in ways towards participants that promote the favoured hypotheses [74]. To address this as best we could, a protocol containing standardised verbal instructions has been developed and used. Therefore, although the experimenter effect cannot be eliminated in its entirety, we hope this strategy, at best, minimises its impact. Regardless, the randomised controlled study design without blinding has its pitfalls, potentially influencing outcomes. Therefore, it must be considered a limitation in the study.

In conclusion, with our study we hope to take the first steps in understanding factors that promote and/or underpin reported health benefits in tinnitus populations who undergo neurofeedback treatment.

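### The last step of offline EEG cleaning is a judgement by eye, and no masking to arm is provided for it, so the ADR-versus-BTR comparison of band power (a secondary outcome) is open to avoidable bias

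*Protocol article*

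**What the plan says.** All references are to the protocol article.

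- **Training outcomes (preprocessing), first step:** "Using a semi-automatic raw data inspection procedure, the recorded data from the training blocks will be screened for artifacts". Numeric limits follow for voltage step, amplitude, within-segment difference and low activity, with 100 ms removed on each side of a detected artefact.
- **Training outcomes, last step:** "A thorough visual inspection will be performed to remove any possible remaining artifacts (i.e., muscle movements and short drifts or jumps". No numeric rule is given for this step.
- **Training outcomes (EEG analysis):** the cleaned data are cut into 2-s epochs and averaged into delta, theta, alpha and beta power for each session and patient.
- **Neurofeedback training groups:** the ADR arm aims at "decreasing the ADR by an increase of alpha [8–12 Hz) and/or a reduction of delta (2–4 Hz"). The BTR arm aims to inhibit theta (4–8 Hz) and/or reinforce beta (13–20 Hz).
- **Randomisation:** an independent researcher performs the allocation and "will subsequently inform the research team about the group allocation of each participant".
- **Discussion:** the study is described as non-blinded, and "we opted for a design in this study in which only participants undergoing neurofeedback are blinded to their intervention".
- **Limitations:** the experimenter effect is acknowledged. The safeguard is that "a protocol containing standardised verbal instructions has been developed and used".
- **Data management and monitoring:** only research-team members who have signed a confidentiality agreement can access the data. "The pseudonymisation allocation list is kept separate from the pseudonymised data".
- **Abstract:** specific power change in the trained bands is listed among the secondary outcomes.

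**The concern.** Once the numeric screen has run, someone decides by eye which further stretches to delete. Deleting more or less alters the band power that remains, and the bands analysed are the ones that the two arms train. If the person deleting knows the arm, strictness could differ between ADR and BTR without intent, and the difference would look like a training effect. If the person also knows the session, the same could happen between early and late sessions.

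At stake is the evidence on whether each protocol changes its own target bands. The Introduction makes specific versus non-specific effects the goal of the study, and it names the link between self-regulated brain activity and outcome as one way to address non-specific effects. Band power feeds that argument.

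**Working it through.** The plan states no figure on this point, so there is none to reproduce. The check is a comparison of the text, followed by an illustration of size.

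**1. Is the step open to judgement?** Yes. The screen has fixed limits. The visual step after it has none, and the plan itself expects artefacts to remain for it.

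**2. Who is blinded?** The Discussion answers this positively: only participants receiving neurofeedback. An EEG rater is not among them.

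**3. Could the rater know the arm?** Randomisation has the research team told each allocation, and Data management limits data access to that team. Together these imply that a rater may know the arm, but no section says who cleans the EEG or what that person sees. The study code hides identity. It is not said to hide arm or session.

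**4. Does the reason for not blinding reach this step?** No. The Discussion argues that double-blinding would require automatic threshold setting, which would impair learning during training. Neurofeedback training groups says that raw signals are stored for later offline processing. By then no threshold is being set.

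**5. Does the stated safeguard reach it?** No. Standardised verbal instructions govern contact with participants, not later deletion of data.

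**6. Which results are exposed?** Band power in ADR versus BTR, and change across sessions. The diary arm has no training sessions. THI and TMI are questionnaires.

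**7. Illustration of size (assumptions, not figures from the document).** Let epoch power follow a gamma distribution with shape *k* and mean 1, and let exactly the highest fraction *q* be deleted. The remaining mean is

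G(x; k+1) / (1 − q), where x is the (1 − q) quantile of the unit-scale gamma with shape *k*, and G(·; k+1) is the distribution function at shape k+1.

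For *q* = 0.05:

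| Shape k | x | G(x; k+1) | Remaining mean | Change |
|---|---|---|---|---|
| 2 | 4.744 | 0.8521 | 0.8521/0.95 = 0.897 | −10.3% |
| 4 | 7.754 | 0.8854 | 0.8854/0.95 = 0.932 | −6.8% |
| 10 | 15.705 | 0.9120 | 0.9120/0.95 = 0.960 | −4.0% |
| 20 | 27.879 | 0.9242 | 0.9242/0.95 = 0.973 | −2.7% |

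Each row compares 5% deletion with none. At shape 4, going from 5% to 10% deletion lowers the mean by a further 5.1%. Each row is the most that removing 5% can do under its shape, because it assumes that the deleted epochs are exactly those with the highest power.

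A second simple model gives a different range. Suppose the share of artefact epochs left in differs by *d* between arms, and each has *r* times the power of a clean epoch. Mean power then shifts by d × (r − 1). With d = 0.05, the shift is 0.05 × 0.5 = 2.5% at r = 1.5 and 0.05 × 4 = 20% at r = 5. Neither *d* nor *r* is in the document. The gap between the two ranges shows that the size depends on the assumptions.

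**The case against.** The strongest case on the other side has five parts.

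- **The rater's knowledge is inferred.** The blinding statement comes in a discussion of treatment delivery, and Limitations speaks of therapists. A condensed article may leave the masking of offline raters to a laboratory manual or analysis plan. It stands that knowledge of arm is not stated for this role. However, the article does more than stay silent: it calls the study non-blinded and says who alone is blinded.
- **The room for judgement is small.** Fixed voltage limits remove large excursions first. Visual removal also comes before the data are cut into epochs, so no one selects epochs by their band power. This stands, and it is why the gamma figures are worst cases.
- **The link to particular bands is not documented.** A reader might infer that the artefacts named are slow drifts lying in the delta band. The text says short drifts or jumps, and it gives no spectrum for these or for the residual muscle activity. The point therefore rests on band power in general, not on a shown overlap with delta or beta.
- **The EEG is not the only training measure.** A reader might take band power to be the trial's sole objective evidence of specificity. Training outcomes also lists mean training level, best run and rewards per session, and the visual step is described only for the offline raw data. The self-reported primary outcomes are untouched, and Limitations already lists the lack of blinding.
- **Renaming files cannot hide the session.** From session 6 a further block with a rising share of transfer trials is added, so a whole-session recording would show whether it is early or late. This stands and changes the fix. Masking the arm remains feasible.

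**Conclusion.** The point holds as a cheap improvement for a secondary outcome. The plan fixes a judgement-based deletion step, limits blinding to neurofeedback participants, and gives a reason for not blinding that does not extend to offline processing. Uneven deletion could therefore bias the ADR-versus-BTR comparison of band power, and change across sessions.

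The documents do not support the stronger reading that the EEG results will be biased, or biased toward the hypothesis by some definite amount. The size and direction cannot be computed from the article. The illustration of about 3% to 10% rests on assumed gamma shapes 20 to 2 and on removal of exactly the top 5% of epochs. The article gives no reference effect against which to judge it. The conclusions on THI and TMI do not depend on this step.

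**What to change.** - Have the independent researcher who holds the allocation list recode the stored raw EEG files, so that the person doing both the semi-automatic and the visual inspection does not see the arm.
- Shuffle the file order and remove session labels where feasible. Full session masking would need recordings cut into blocks, because the transfer block from session 6 is recognisable.
- Lock the cleaned data before unmasking.
- Report the percentage of data removed by arm and session.
- Add a sensitivity analysis of band power using only the fixed-criteria screen.

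If raters are already masked to arm, one sentence saying so would settle the masking part.

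Cost: a little extra file handling and one extra analysis. There is no burden on participants, and because the raw signals are stored, the change can be made after recruitment has started.

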#### Data management and monitoring

Upon registration on the web platform, participants are assigned a computer-generated study code, which will follow them throughout the trial. All collected data are stored and pseudonymised in locked cabinets or as computer files. The pseudonymisation allocation list is kept separate from the pseudonymised data and deleted upon completion of the trial. Participants will be informed of this procedure. Only people who have signed a confidentiality agreement and are part of the research team have access to the data collected in the study.

The study’s assessment questionnaires are answered online. All necessary precautions have been taken to ensure data protection and security. All data exchanged between participants and the online system are encrypted prior to transmission and storage. The online system is managed and hosted by the IT Department of Linköping University (Sweden). No entries in the form of video or sound recordings, which could make it possible for third parties to identify the participants, are registered. Until the pseudonymisation allocation list is deleted, participants can ask for their data to be deleted at any time upon stating their assigned code. Lastly, data collected during the study are kept for 10 years before being deleted.

### Adverse events

Neurofeedback is generally considered safe and involves no risk to participants [60]. This is perhaps best reflected in the fact that it has been used extensively in studies involving children with ADHD. Thus, participants in our trial should not experience more serious side effects than perhaps mild headaches, stemming mainly from the prolonged period of sustaining attention during training. Nevertheless, the adverse effects of neurofeedback training will be routinely monitored as part of the ongoing dialogue between data collectors and trial participants. In the unlikely event that a trial participant complains about serious adverse effects as a result of the training, data collectors will, as a first step, reduce the frequency of training sessions in the week of the complaint and, if needed, reduce the number of training segments per training session until the trial participant no longer complains about adverse effects.

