**Fig. 1 Fig1:**
[figure not shown]
Schedule of enrolment, interventions and assessments

The fourth and final stage in t0 is a standard audiological examination at the ENT-clinic at the University Hospital of Giessen and Marburg (UKGM). There are two main purposes for this visit: The first is to rule out possible non-subjective causes of tinnitus, and the second, to acquire audiometric data. At the clinic, participants first learn about the components of the audiological examination before signing the informed consent form (see Additional file 5). Subsequently, the audiological examination, in which the below information is acquired, takes place:
Standard Audiogram (to 20.000 Hz)TympanometryOtoacoustic emission (OAE)Tinnitus loudness discomfort levelTinnitus matching (loudness, pitch)

Participants who are included after the visit to the ENT clinic take the baseline assessment in the pre-allocation (t1) stage. Upon completion of this assessment, participants move to the allocation (t1) stage and are randomly assigned to one of three arms in the study: Group 1, which receives alpha/delta neurofeedback training; Group 2, which receives beta/theta neurofeedback; and Group 3, which is the diary control group.

The post-allocation (t2) intervention period lasts 4 weeks. Within this timeframe, ten neurofeedback training sessions are undertaken for the two neurofeedback groups, with a minimum of two and maximum of three sessions per week. For the diary control group, two face-to face visits to the department and two telephone calls are scheduled within the 4-week period. t2 mid-point assessments are completed 2 weeks after the start of the intervention. In the post-allocation (t3) stage, participants complete the endpoint assessment online prior to a visit to the Department of Psychology, where they complete the ANT and SART (referred to as cognitive assessment II in Fig. 1). t3 post-assessments are completed 4 weeks after the start of the intervention.

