The t4 follow-up takes place 4 months after the start of the intervention. Here, participants in the neurofeedback groups complete assessments online before coming to the Department of Psychology for a booster neurofeedback session. The booster sessions serve the practical goal of probing the participants about their experiences with neurofeedback. Moreover, the visit is included to increase the likelihood of participant adherence to questionnaire completion. For diary control participants, t4 assessments are completed 4 months after the start of the intervention. As a token of appreciation, they then receive a copy of a self-help book on tinnitus [29].

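### Adverse effects are monitored only as effects of neurofeedback, in conversations that are more frequent in the neurofeedback arms, so complaints such as headache cannot be compared fairly with the diary arm

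*Protocol article*

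**What the plan says.** The Adverse events section describes one method: "the adverse effects of neurofeedback training will be routinely monitored as part of the ongoing dialogue between data collectors and trial participants". The one harm it names as plausible is mild headache. The same data collectors also act on the training schedule: if a participant complains of serious effects, "data collectors will, as a first step, reduce the frequency of training sessions in the week of the complaint".

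The contact schedule is under Procedure/trial protocol. In the 4-week intervention period, "ten neurofeedback training sessions are undertaken for the two neurofeedback groups, with a minimum of two and maximum of three sessions per week". In the diary arm, "two face-to face visits to the department and two telephone calls are scheduled within the 4-week period". The Diary control group section describes those calls as supportive and concerned with the diary exercise. At t3 participants visit the department for the cognitive tests, with no restriction by arm. At 4 months, "participants in the neurofeedback groups complete assessments online before coming to the Department of Psychology for a booster neurofeedback session", and that visit is used to ask about their experience of neurofeedback. For the diary arm only the assessments are stated at that point.

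On blinding, the Discussion says that "only participants undergoing neurofeedback are blinded to their intervention". The Limitations section adds: "The non-blinding of therapists in the neurofeedback conditions mean the outcomes are more susceptible to the experimenter effect".

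**The concern.** Two features of the stated method work against a comparison with the diary arm.

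- **What is collected.** The target is effects of training. Diary participants have no training, so a headache in that arm has no place in the monitoring as described. Headache is common without any intervention, and a rate in the neurofeedback arms cannot be interpreted without a rate in people who were not trained.
- **How often there is an occasion to report.** Complaints arise in conversation, and conversations are scheduled more than twice as often in the neurofeedback arms. More occasions produce more reports even if the true rates are equal.

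The staff who hear the complaints are also not blinded, and the wording invites them to judge whether training was the cause.

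The Introduction and the Discussion base the three-arm design on subtracting the diary arm to isolate non-specific effects. A reader will want to do the same for tolerability. The Introduction also says that no tinnitus study has used the BTR protocol, so there is no earlier tolerability experience in this population to fall back on.

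**Working it through.** The protocol gives no figure for harms, so there is none to reproduce. The check counts contacts and then asks how far unequal contact alone could separate the arms.

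**Scheduled contacts per participant** (from Procedure/trial protocol)

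| Period | ADR | BTR | Diary | Neurofeedback : diary |
|---|---|---|---|---|
| Intervention only | 10 | 10 | 2 + 2 = 4 | 10/4 = 2.5 |
| Plus t3 visit | 11 | 11 | 5 | 11/5 = 2.2 |
| Plus 4-month booster visit | 12 | 12 | 5 | 12/5 = 2.4 |

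The t3 row assumes that the cognitive-test visit applies to all arms and is separate from the diary arm's two visits, which is the natural reading. The ratio of ADR to BTR is 1.0 in every row, because the Randomisation section gives both arms the same number, duration and intensity of sessions.

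**Effect of unequal contact when true rates are equal.** Let q be the chance that a participant with a background complaint mentions it at any one contact. The documents give no value, so q is an assumption and a range is shown. Contacts are treated as independent. The share reporting at least once is 1 − (1 − q)^contacts.

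For q = 0.05 with the intervention contacts alone: 1 − 0.95^10 = 0.401 and 1 − 0.95^4 = 0.185.

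| q (assumed) | 10 contacts | 4 contacts | Ratio | 11 contacts | 5 contacts | Ratio |
|---|---|---|---|---|---|---|
| 0.05 | 40% | 19% | 2.2 | 43% | 23% | 1.9 |
| 0.10 | 65% | 34% | 1.9 | 69% | 41% | 1.7 |
| 0.20 | 89% | 59% | 1.5 | 91% | 67% | 1.4 |
| 0.50 | 99.9% | 94% | 1.1 | 99.95% | 97% | 1.0 |

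Counting the t3 visit softens the imbalance but leaves it in place. It is large when complaints are mentioned only occasionally, as is likely for mild, unprompted symptoms, and nearly vanishes when q is high.

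This calculation supposes that diary complaints are recorded on the same terms as the others. The wording of the Adverse events section does not provide for that, so the table isolates the effect of frequency and does not describe the whole problem.

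**The case against.** The strongest reply is that this is a condensed article. Recording forms and harms tables usually sit in the full protocol, and the article states no objective of comparing harms between arms. That stands in part: the absence of a form here is no fault. But the article does state a method, and a fuller document would have to replace that wording, not merely add detail to it. The numbers above also depend on an assumed q.

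Four stronger readings are tempting, and the text does not support them.

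- **That collection ends at week 4.** The section calls the dialogue ongoing and sets no end, and the 4-month visit asks neurofeedback participants about their experiences. What the text shows is that this later visit is stated for two arms and not for the third.
- **That harms cannot be compared across any of the arms.** ADR and BTR share the same schedule and the same participant blinding. Contact frequency cannot bias that contrast. Unblinded staff remain a risk there, and the Limitations section already acknowledges therapist non-blinding as a source of bias in the outcomes.
- **That worsening tinnitus in the diary arm goes uncollected.** THI, TMI, TFI, ISI and PHQ-9 are self-reported outcomes, and the Statistical analysis section models all outcomes by group and time. Worsening of tinnitus, sleep or mood is therefore measured in every arm without staff judgement. What is missing in the diary arm is mainly complaints outside these scales, such as headache.
- **That attribution to training is a formal condition for being counted.** No counting rule is given. Attribution enters through the way the target is described.

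It is also an inference that the data collectors are the trainers. They adjust the sessions, but the text does not call them trainers.

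**Conclusion.** The point holds for neurofeedback versus diary, and for complaints that the outcome questionnaires do not cover. As stated, the method yields no background rate for these in the diary arm. Even if diary complaints were recorded informally, unequal contact (about 11 against 5 through t3) would bias the comparison towards more reported harm under neurofeedback. With equal true rates and the intervention contacts alone, the spurious difference runs from 40% against 19% at q = 0.05 to 99.9% against 94% at q = 0.50. These figures illustrate the direction and possible size of the bias. They are not estimates, since q is assumed and contacts are treated as independent.

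For ADR versus BTR the concern reduces to staff who know the allocation. The efficacy analysis is not affected by this point. It is worth correcting because the remedy is cheap and part of it needs no new data.

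**What to change.** 1. **Use what is already collected.** Report by arm, for t2, t3 and t4, the number of participants who deteriorate from baseline on THI, TMI, PHQ-9 and ISI. The amount of change that counts as deterioration should be fixed before the data are examined. The cost is one table and no participant burden.
2. **Ask everyone the same question.** Add one short, identical item set to the online assessments still to be completed (t2, t3, t4) in all three arms. Word it without reference to cause, for example headache, fatigue and any other new or worse complaint. Use it for the between-arm harms comparison.
3. **Keep the dialogue, but separately.** Report complaints raised with data collectors as a non-comparative source, and say so in the Adverse events section.

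The item set costs one to two minutes per questionnaire, and prompted questions will bring out more minor events in every arm. Its reach is limited by timing. The protocol version is dated 17 March 2020, with recruitment running from 1 November 2018 to an expected end in June 2020, so most participants will lack the early time points. Counting back 4 months, those who started the intervention after about mid-November 2019 could still answer at t4. For everyone else the deterioration table is the only comparable source, and the report should state this.
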